### Study population

Patients are selected based on the following inclusion criteria: 1) post-bronchodilator FEV_1_/FVC ratio < 70%; 2) age > 40 years; 3) smoking history of more than 20 years or 15 pack-years; 4) diagnosis of COPD as major functionally limiting disease and 5) current use of bronchodilator therapy. Exclusion criteria are: 1) primary diagnosis of asthma (onset < 35 years, ≥ 12% post-bronchodilator reversibility); 2) primary diagnosis of cardiac disease and 3) presence of disease that could either affect mortality or participation in the study (e.g. confusional states).

### Recruitment and informed consent

Patients are recruited from seven regional hospitals and five general practices in the Netherlands. Inclusion takes place within a period of 5 months (winter - spring). Medical records of patients with a scheduled visit to a respiratory nurse or practice nurse (from here referred to as respiratory nurse) are screened for in- and exclusion criteria by a respiratory or family physician. Eligible candidates receive an information letter about the content of the study two weeks prior to a scheduled (regular) visit to the respiratory nurse (figure 1) including an informed consent form. One week before this visit, patients are contacted by telephone by one of the researchers to get their permission to send a baseline assessment questionnaire and to provide additional information when needed. The informed consent form and baseline questionnaire are turned in at the visit to the respiratory nurse.

**Figure 1 F1:**
[figure not shown]
**Schematic overview of the study procedure**. Patients are recruited and informed, two weeks before randomization. R: Reinforcement of AP use by telephone, only for the intervention group.

### Control group

Usual care consists of both pharmaceutical and non-pharmaceutical care according to most recent evidence-based guidelines on COPD care[1]. At inclusion all patients are seen by a respiratory nurse who systematically checks and discusses the following aspects of COPD care: vaccination, optimizing medication, inhalation techniques, exercise, nutritional aspects, smoking (cessation) and exacerbation management. When needed, additional instructions or information is provided including information booklets, referral to a physiotherapist, dietician etc. To control for any co-intervention, all nurses are asked to record the different aspects discussed in this session. During follow-up, patients have normal access to their physician and respiratory nurse. No attempts are made to change the frequency of scheduled visits.

### Intervention

In addition to care as usual, patients in the intervention group receive an individualized Action Plan. The first version of the AP was developed using a combination of the Anthonisen classification of exacerbation symptoms and signs[20], and the AP used by Watson et al[21]. To optimize the AP for disease-related patient utilization and to guarantee that the AP does not conflict with evidence-based guidelines on COPD care, five experts in the field of COPD self-management (n = 3) and COPD guidelines (n = 2) were consulted using semi-structured interviews. With the resulting version of the AP a pilot study was conducted from December 2007 until May 2008. In this study, 121 (response rate 71%) COPD-patients (age 67.4 ± 10.5 years, FEV_1 _47.7 ± 18.5% pred) received an AP and were followed up for 42 days. Thirteen patients were lost to follow-up (11%). Patients reported both format and content of this AP as highly satisfactory. In this pilot study we acquired experience and understanding in patient recruitment, patient response, study procedures in self-management research, daily diary symptom assessment/analysis and patients' perception of AP use.

The final version provides a colour-coded overview of patients' stable and deteriorated symptom status related to individualized pharmaceutical and non-pharmaceutical treatment prescriptions. The backside of the AP includes three sections which can be used to provide additional (individualized or general) information on medication, exercise and nutrition. The AP is printed on A3-sized paper and folded as a brochure. Standardized instructions on how to use the AP are provided by the respiratory nurse. An information brochure is provided as well. In addition the AP is individualized by the respiratory nurse together with the patient by filling in 1) a list of important contact persons and telephone numbers; resource persons: family physician, respiratory physician and respiratory nurse; 2) stable symptom severity (individual stable/normal green zone symptom status); 3) regular medication/lifestyle prescriptions (green zone); 4) additional medication/breathing exercises and energy preservation in case of symptom increase (yellow zone, orange zone); 5) name contact person/telephone number in case of an exacerbation (orange zone)

The AP is clearly not a one-moment 'paper' intervention. After being instructed on the individualized AP content and use, the patient is instructed to bring the AP to every visit to a healthcare provider. In these follow-up visits, the AP can be changed or made complete. Within the study period, there will be two standardized reinforcement sessions by telephone at 1 and 4 months, performed by an independent respiratory nurse (figure 1). In these sessions, patients understanding and adherence concerning AP use is evaluated and when needed additional information is provided.

### Outcomes and measurements

#### Exacerbations

Exacerbations are detected by daily recording of symptoms. Symptoms recorded are termed major and minor (figure 2) according to Anthonisen et al[20]. A symptom-based exacerbation is defined by the onset of two or more new or deteriorated symptoms, of which at least one major symptom, persisting for 48 hours or more. A subsequent exacerbation is defined as a new event only in the presence of at least two stable weeks. Exacerbation onset is defined by the first day on which the symptom criteria are met. Daily symptoms are binary coded and summed to give a daily symptom count. Major are scored as: normal = 0; small increase = 1; or clear increase = 2. The minor symptoms are scored 0 and 1 respectively. Adding all these scores results in a daily symptom count with a range from 0-11 points. Exacerbations are recovered when the three-day moving mean of the symptom count returns to the symptom count of days fourteen to eight prior to exacerbation onset.

**Figure 2 F2:**
[figure not shown]
**Symptom-based exacerbation algorithm according to Anthonisen et al**.

#### Primary outcome

##### Health status recovery time

The Clinical COPD Questionnaire (CCQ) score is used to measure disease-related health status. The CCQ is a validated ten-item questionnaire, divided into three domains: symptoms, functional state and mental state[22]. In this study the 24-hour version is used, in which patients are asked to record their experiences during the last 24 hours. Recovery time of health status in the event of an exacerbation is defined by the number of CCQ units from the onset of a symptom-based exacerbation, up to the moment CCQ score is back to its pre-exacerbation average (figure 3). If a patient does not fully recover from an exacerbation, the CCQ-recovery time is defined by the onset of the exacerbation and a new stable condition, deflected by discontinuation of recovery for three consecutive units. A new stable condition is present when the standard deviation of the new baseline is less than the pre-exacerbation three units' standard deviation.

**Figure 3 F3:**
[figure not shown]
**CCQ recovery time**. Example of CCQ recovery time in a patient with full recovery (A) and a patient who does not fully recover but has a new baseline (stable) condition after 9 days = 3 units (B).

#### Secondary outcomes

##### Symptom recovery time

Symptom recovery time is calculated as the number of days from exacerbation onset for the 3-day moving average of the exacerbation daily symptom count to return to the mean symptom count on day fourteen to eight preceding exacerbation onset. The use of a 3-day moving average minimises the effect of day to day variations without biasing the results[12].

##### Health-related quality of life

The St George Respiratory Questionnaire (SGRQ) is used to measure health-related quality of life (HRQL). It is validated for measuring health impairment in COPD patients. The SGRQ consists of sixteen questions in three domains: symptoms, activity and impact. It assesses patients' perception of respiratory problems over a preceding period, ranging from one month to one year, as well as their current state[23]. Both between group differences in SGRQ scores will be assessed as well as the proportion of patients crossing the clinical relevant threshold of 4 points [24].

##### Unfavourable health status

Unfavourable health status days per patient-year is defined as the number of days on which the CCQ score is = the individual CCQ-score mean (total follow-up time) minus one standard deviation. Each patients' score is divided by their follow-up time (patient - year).

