## Methods

### Design

The study is conducted as a single-blind randomised controlled trial, with a 6 months follow-up. Patients are randomly assigned to either care as usual or treatment with an individualized AP as an addition to care as usual. The randomisation procedure is performed by a respiratory nurse (RN). To conceal the assignment sequence, a central web-based service on a 1:1 basis is used. Randomisation is stratified by centre and gender.

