#### Follow-up assessment

Patients are instructed to record any increase in a predetermined list of symptoms over their chronic (stable) symptoms during the previous 24 hours. Every third day the CCQ is completed. Patients receive six diary booklets, each consisting of 30 days. After completing one of the diaries, patients are asked to send them to the investigator. Every four weeks patients are contacted by telephone to assess healthcare utilization and to evaluate proper use of the diary. At 24 weeks, HRQL, anxiety and depression, dyspnoea and self-efficacy are reassessed. After filling in the last diary and follow-up questionnaire, patients receive a postponed-information letter about the aim of the study and AP and their allocation. Additional data regarding health care consumption (exact date and content of visits and interventions) are obtained from medical records.

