### Sample size

Based on two studies, a median health status recovery time around 12 (IQR 8-16) days is expected [9,27]. Unfortunately we do not know the shape of the underlying distribution. Nevertheless, a nonparametric test might require either more or fewer subjects compared to a Students' t-test, but they never require more than 15% additional subjects if 1) the number of subjects is reasonably high: (how high depends on the nature of the distribution and test, but figure at least a few dozen) and 2) the distribution of the data is not unusual (does not have infinite tails, in which case its standard deviation would be infinitely large)[28].

Hence, we adopted the general rule for computing the sample size required for a t-test. In a normal distribution the distance between the first quartile and the median is approximately 0.67 times the standard deviation of the distribution. Thus, if we assume the distribution of recovery time (median = 12, IQR = 8-16) to be normal, the mean of this distribution will be 12, with standard deviation 6. Sample size is calculated based on the smallest detectable change of one 3-day CCQ unit. Using the aforementioned 15%-rule, would mean a sample size of 63 (two tailed t-test) * 1.15 (+ 15%) = 73 exacerbations are needed in both arms to have an 80% chance of detecting a difference, using a two side alpha = 0.05.

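### Unfavourable health status days are counted against each patient's own on-study CCQ mean and SD, so the count cannot register a change in CCQ level or spread and does not rank exacerbation burden reliably

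*Protocol article*

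**What the plan says.** Under Unfavourable health status, the protocol article counts "the number of days on which the CCQ score is = the individual CCQ-score mean (total follow-up time) minus one standard deviation" and divides by the patient's follow-up time. The comparison sign prints as an equals sign. It is probably an inequality lost when the text was read, and nothing below depends on it.

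The scores come from the diary: "Every third day the CCQ is completed" (Follow-up assessment). The trial runs "with a 6 months follow-up" after random assignment (Design), so the whole period that supplies the mean and SD is on-study. CCQ is not among the parameters listed under Baseline assessment.

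The other recovery outcomes use a different kind of reference. CCQ recovery time refers to the patient's average before the exacerbation, and symptom recovery time to days fourteen to eight before onset. Only the unfavourable-days outcome uses a reference that contains the bad periods it is meant to count.

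**The concern.** A threshold at a patient's own mean and SD standardises that patient's scores before they are counted. Level and spread are removed, and only the shape of the distribution can affect the result. A patient who is better throughout follow-up gets the same count as one who is worse throughout. Exacerbations also move the mean and inflate the SD, so they partly hide themselves.

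At stake is the reading of one secondary outcome. A result near zero could be reported as no effect on health status when the measure could not have shown an effect on level. A patient freed of exacerbations could even be credited with more unfavourable days than before.

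**Working it through.** The article gives no expected value for this outcome, so there is no stated figure to reproduce.

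**Inputs from the article:** a CCQ every third day in six 30-day diaries (180 / 3 = 60 scores per patient); recovery time 12 days, SD 6; a target difference of one 3-day unit (12 to 9 days); 2.53 to 5.0 exacerbations per patient-year (Sample size).

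**Assumed, not in the article:** an exacerbation step of 1.0 CCQ point, and normal within-patient noise with SD s from 0.1 to 0.5 (0.1 to 0.6 in step 3).

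**1. Invariance (no assumption needed).** Let y' = a + b·y with b > 0. Then mean' = a + b·mean and SD' = b·SD, so y' ≤ mean' − SD' exactly when y ≤ mean − SD. The same holds for mean + SD and for either direction of the inequality. In one test series of 60 scores there were 11 upper-tail and 7 lower-tail scores before, after a shift of −0.5, and after halving every score.

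With purely normal fluctuation the share beyond one SD is Φ(−1) = 0.159 at any mean and SD, and 0.159 × 365 = 58 days a year.

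**2. Exacerbation time.** Let a fraction p of follow-up be raised by 1.0. Taking the stable level as 0, m = p and D = √(s² + p(1 − p)).

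- Lower tail: (1 − p)·Φ((m − D)/s) + p·Φ((m − D − 1)/s)
- Upper tail: (1 − p)·[1 − Φ((m + D)/s)] + p·[1 − Φ((m + D − 1)/s)]

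Example, s = 0.3 and p = 0.10: D = √(0.09 + 0.09) = 0.424. The lower tail is 0.9·Φ(−1.08) plus a negligible term = 12.6%.

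Share of days (%) at p = 0 / 10 / 20 / 30%:

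| s | lower tail | upper tail |
|---|---|---|
| 0.1 | 15.9 / 1.4 / 1.3 / 3.2 | 15.9 / 10.0 / 20.0 / 29.7 |
| 0.2 | 15.9 / 8.7 / 8.7 / 11.1 | 15.9 / 10.9 / 19.3 / 25.2 |
| 0.3 | 15.9 / 12.6 / 12.7 / 14.3 | 15.9 / 13.1 / 17.6 / 21.0 |
| 0.4 | 15.9 / 14.3 / 14.4 / 15.4 | 15.9 / 14.4 / 16.6 / 18.5 |
| 0.5 | 15.9 / 15.0 / 15.2 / 15.8 | 15.9 / 15.1 / 16.2 / 17.3 |

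Simulation with 60 scores per patient at s = 0.3 gave 15.9 / 12.4 / 12.4 / 14.1 and 15.9 / 13.0 / 17.7 / 21.1, in close agreement. In every row, both tails give a patient with no exacerbations a higher count than one exacerbating 10% of the time.

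**3. The trial's own target effect.** This simulation used 3 exacerbations a year, each with a peak of 1.0 point that declines over the episode, and mean duration cut from 12 to 9 days. True exacerbation days fall from about 33 to 25 a year. Counted days per year:

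| noise SD | lower tail | upper tail |
|---|---|---|
| 0.1 | 26.5 → 27.5 | 44.5 → 39.5 |
| 0.2 | 46.8 → 47.3 | 50.4 → 48.4 |
| 0.4 | 55.9 → 56.2 | 56.4 → 56.1 |
| 0.6 | 57.6 → 57.4 | 57.6 → 57.6 |

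The lower tail is flat or moves slightly the wrong way. The upper tail falls clearly only when noise is small. With no exacerbations at all, both tails give about 58 at every noise level.

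**4. Contrast with a fixed threshold.** With s = 0.3 and a threshold 0.5 above the common stable level, the share is (1 − p)·[1 − Φ(0.5/0.3)] + p·Φ(0.5/0.3). This gives 4.8 / 13.8 / 22.9 / 31.9% at p = 0 / 10 / 20 / 30%, in the right order throughout.

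**The case against.** The strongest defence is that the Action Plan aims to shorten exacerbations, which changes the shape of a patient's scores rather than shifting them permanently, and that an upper-tail count can pick this up. The article's rates times 12 days give 2.53 × 12 / 365 = 8% to 5.0 × 12 / 365 = 16% of time in exacerbation. Over that range the upper-tail share rises from 12.6% to 15.9% at s = 0.3, and from 9.8% to 16.2% at s = 0.2.

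This stands. A reader might infer that the count comes out about the same whatever treatment does, or that the outcome cannot show any benefit. The documents do not support that: the invariance is exact for level and spread only. The defence does not rescue the measure, however. It depends on the upper tail and on small noise, and the ordering fails against patients with no exacerbation. The Sample size section assumes 70% of patients have at least one, which leaves up to 30% with none.

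A reader might also infer that the plan counts the best days rather than the worst. That is so only if higher CCQ is worse and the lost sign means at or below. The article states neither, so this is a request to state the direction, not an established error. If the sign means at or above mean minus SD, the count covers about 84% of days under normal fluctuation and is equally invariant.

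Finally, the consequences are limited. The outcome is not named among the secondary objectives and carries no sample size, and overall health impairment is also measured by the SGRQ. This too stands.

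**Conclusion.** The definition is wrong as written, for one secondary outcome. That it cannot register an effect on CCQ level or spread follows from algebra and needs no assumption.

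That it misorders exacerbation burden rests on the assumed 1.0-point step, normal noise and s between 0.1 and 0.5. Under these, a patient with no exacerbations scores about 58 days a year. A patient exacerbating 10% of the time scores about 5 to 55 on the lower tail (1.4% to 15.0% of 365) and 37 to 55 on the upper (10.0% to 15.1%). Above about 10% the upper tail rises with burden, clearly when noise is small and weakly when it is large. The lower tail does not track burden at any noise level examined.

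The primary outcome, with its pre-exacerbation reference, and the sample size are not affected.

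**What to change.** Replace the outcome with the patient's time-averaged CCQ, that is, the area under the 3-day CCQ curve divided by follow-up time. Compare it between arms with adjustment for centre and gender, the stratification factors. This keeps the level of health status. It is a different quantity from a day count, and the text should say so.

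If a day count is kept, state which direction of the CCQ is worse and print the inequality. Count days on which CCQ is worse than a threshold that is fixed in advance, identical for all patients, and not derived from the patient's own follow-up mean and SD. A reference taken from the first diary is not a clean substitute: CCQ is not among the listed baseline parameters, so that diary is itself post-randomisation and could already reflect the Action Plan or an early exacerbation. Use it only with that limitation stated.

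The cost is a rewritten definition of one secondary outcome, using CCQ data the trial already collects.

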##### Anxiety and depression

The Hospital Anxiety and Depression Scale (HADS) is used to measure symptoms of anxiety and depression. Both domains consist of seven statements on emotions or emotional situations. Patients express their agreement with the statements on a scale from 0 to 3, which leads to a maximum score of 21 points for each domain. Scores between 8 and 11 per domain are suggestive of the presence of the mood disorder; scores = 11 indicate a probable presence[25].

##### Self-efficacy

Exacerbation-related self-efficacy is measured by a self-developed questionnaire, consisting of 11 items. Patients are asked to grade their confidence in their own self-management capabilities in the occurrence of an exacerbation on a 5-point Likert scale. Lower scores indicate high confidence in adequate exacerbation related self-management behaviour. No data is available on validity and responsiveness of this questionnaire, this will be addressed simultaneously to the current study.

##### Treatment delay

Number of days between the onset of an exacerbation and initiation of antibiotics or oral corticosteroids.

##### Exacerbation rate

• Proportion of patients that experience a symptom-based exacerbation.

• Proportion of patients that experience an event-based exacerbation, i.e. the occurrence of an exacerbation for which antibiotic or corticosteroid treatment is initiated.

• Number of symptom-based exacerbations per patient year, by dividing each patients' exacerbation rate by their follow-up time.

• Number of event-based exacerbations per patient year, by dividing each patients' exacerbation rate by their follow-up time.

##### Health care utilization and cost-effectiveness

The number of respiratory-related hospital admissions, hospital days, emergency room visits and scheduled and unscheduled visits or telephone calls to both respiratory and family physicians are assessed. The proportion of patients having one or more respiratory-related hospital admissions is determined, as well as the number of days between inclusion and first hospital admission.

The perspective of the healthcare payer is adopted for the cost-effectiveness analysis (CEA). Resource use is valued in monetary terms by multiplying the units consumed by the cost per unit[26]. Two major cost categories are distinguished: program implementation and direct health care. Data on cost and outcome are brought together to estimate incremental cost-effectiveness ratios (ICERs) and subsequently calculated as costs per exacerbation-related CCQ unit prevented, per hospital admission prevented, and per health care contact prevented. Sensitivity analysis is used to test the cost-effectiveness model for methodological uncertainty and generalizability.

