***Statistics***				
Follow-up (mths)	6	6	12	12
n		56	102	151
Powered on	Δ exa-rt = 1	Δ SGRQ = 5.7	Δ SGRQ = 4	Δ SGRQ = 4
SSC	245	124	124	160

OC, outpatient clinic; GP, general practice; exa-rt, exacerbation recovery time; SGRQ, St George respiratory questionnaire n, number of patients; SSC, sample size calculation; pt, patient; inv, investigator.

Usually, blinding in self-management or educational interventions is nearly impossible, but the so called 'modified informed consent' procedure, does enable a single-blind RCT and consequently compensates for substantial threats to internal validity. In the field of disease management research this can be regarded innovative in terms of methodology.

In the studies of Wood-Baker et al[34] and McGeoch et al[35], randomization was clustered to prevent cross-contamination of educational messages within a practice. Selection bias in cluster randomized trials may threaten the validity of the results. These studies however did not inflate their sample size to accommodate for this clustering effect [36]. We believe that in this robust study (245 patients) the impact of contamination is regulated by the modified informed consent procedure (patient not knowing that the AP is part of the study objective) and the strict instructions of RN's not to inform control patients about the existence of the AP. The remaining threat of contamination does not weigh against the disadvantage of the huge sample size needed in a clustered trial to compensate for the high inter-cluster variations in both patient (i.e socioecomic differences) and healthcare (i.e. number and content of respiratory nurse consultations) characteristics.

Although all studies used an individualized AP, aimed at early recognition of exacerbations, there are some differences between the interventions. Instead of encouraging self-initiation of antibiotics or oral corticosteroids, the AP used in the current study aims at early contact with a healthcare provider only. The choice to initiate pharmaceutical treatment is left to the physician. Moreover, we have respiratory nurses to evaluate use of the AP and provide additional information when needed. Reinforcement has shown to be essential in changing self-management behaviour, leading to better use of the intervention [37].

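### The utilisation outcome lists visits and calls to physicians but not to the respiratory nurse, whom the Action Plan names as a resource person, and the contact in the cost-effectiveness ratio is undefined

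*Protocol article*

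**What the plan says.** All references are to the protocol article.

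- **Health care utilization and cost-effectiveness.** The utilisation items are respiratory-related admissions, hospital days and emergency room visits, followed by this outpatient item: "scheduled and unscheduled visits or telephone calls to both respiratory and family physicians are assessed". No nurse contact appears. The cost-effectiveness analysis takes the healthcare payer's view and includes ratios "per hospital admission prevented, and per health care contact prevented". On costs: "Two major cost categories are distinguished: program implementation and direct health care". Neither the contact nor the direct-care category is broken down by type of provider.
- **Intervention.** The nurse completes the Action Plan with the patient, and it lists "resource persons: family physician, respiratory physician and respiratory nurse". Its orange zone also carries the name and number of a person to contact in an exacerbation, whose profession is not stated. Two reinforcement calls, at 1 and 4 months, are made by an independent respiratory nurse.
- **Control group.** "During follow-up, patients have normal access to their physician and respiratory nurse".
- **Discussion.** "the AP used in the current study aims at early contact with a healthcare provider only". The decision to start drug treatment stays with the physician.
- **Follow-up assessment.** Utilisation is asked about by telephone every four weeks. Dates and content of visits come from medical records. Neither source is limited to physicians.

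**The concern.** The outcome list is specific: it separates scheduled from unscheduled contacts, includes telephone calls, and names two kinds of physician. It leaves out the provider who issues the Action Plan and whom the plan names as a contact. Nurse access exists in both arms, but only intervention patients hold a document that points them to the nurse, so any undercount need not be equal between arms.

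Two results are at stake: the between-arm comparison of healthcare contacts, and the cost-effectiveness analysis. In the latter, the contact count is the denominator of one ratio, and direct-care cost enters the numerator of all of them. An intervention designed to prompt early contact should be judged by a measure that records contact with every provider it can prompt patients to approach.

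**Working it through.** The article states no contact rate, so there is no planned figure to reproduce. The check compares the passages and then works out what the listed count would miss.

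**1. Providers counted against providers named**

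| Provider | Resource person on the Action Plan | Visits and calls listed in the outcome |
|---|---|---|
| Family physician | yes | yes |
| Respiratory physician | yes | yes |
| Respiratory (or practice) nurse | yes | no |

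The Recruitment section uses the term respiratory nurse for practice nurses too, so the gap covers hospitals and general practices alike. The Discussion also gives variation in the number and content of nurse consultations as a reason against cluster randomisation. Nurse contact is thus treated elsewhere as a material and variable part of care.

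**2. What the omission does to the comparison**

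Let P be physician contacts and N nurse contacts per patient, with subscript C for usual care and A for the Action Plan.

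- Contacts prevented, all counted: (P_C + N_C) − (P_A + N_A)
- Contacts prevented, listed only: P_C − P_A
- Error (listed minus all): N_A − N_C

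The listed count overstates contacts prevented by exactly the excess of nurse contacts in the Action Plan arm. Three cases follow.

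- *Equal nurse use* (N_A = N_C): the error is zero.
- *Substitution* (a share s of C physician contacts moves to the nurse, total unchanged): the true number prevented is 0, and the listed number is C × s.
- *Addition* (the nurse is called as well as the physician): P_C − P_A is 0, so nothing is falsely scored as prevented, but the extra nurse contacts and their cost do not appear.

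**3. Illustration of the substitution case**

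C and s are assumptions; the article gives neither.

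- C = 2, s = 10%: 2 × 0.10 = 0.2 per patient, or 20 per 100 patients
- C = 4, s = 25%: 4 × 0.25 = 1.0 per patient, or 100 per 100 patients
- C = 6, s = 50%: 6 × 0.50 = 3.0 per patient, or 300 per 100 patients

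The range restates the inputs and is not an estimate for this trial.

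**4. Reinforcement calls**

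If nurse contacts were added to the list without distinction, the two protocol calls would add 2 contacts to each Action Plan patient who received both and none to controls. They have to be kept apart from care-related contacts.

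**The case against.** A reader might infer that nurse contacts are scored as prevented. The article does not say so. The ratio refers to healthcare contacts without restricting them to physicians, direct health care has no provider limit, and the effect follows only if both are read through the physician list. The point is conditional for that reason.

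A reader might also infer that contacts will move to the nurse. No shift is shown. The plan names two physicians beside the nurse, the orange-zone contact may be any of them, and a patient who needs drug treatment must still reach a physician. Nurse contact may therefore add to physician contact instead of replacing it. Control patients can reach the nurse as well, so the omission touches both arms and could cancel.

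Nor can one say that contact patterns could not be reconstructed by arm. The four-weekly calls and the record review are worded broadly enough to capture nurse visits. Nurse telephone calls are less clearly covered, since the record review mentions visits and interventions only. Treatment delay is measured separately, from diary-defined onset to the start of antibiotics or oral corticosteroids.

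Finally, an article may leave itemised resource use to the full protocol. That would answer the point if the article were silent, but it gives an explicit list, and the list omits one of the three providers the intervention names. The undefined contact matters mainly because this list is the only definition on offer.

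The qualifications on certainty and size stand. The omission itself is not answered by any of them.

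**Conclusion.** The point holds as a conditional one. As written, the utilisation outcome misses a contact channel that the intervention itself can drive. If the contact in the cost-effectiveness ratio and the direct-care costs follow the same list, substitution toward the nurse would look like prevention and added nurse contact would go uncosted. Both would favour the Action Plan if its patients use the nurse more than controls do; equal use would leave no error in the difference.

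The size is N_A − N_C contacts per patient, and the article gives no basis for estimating it. The 0.2 to 3.0 shown above depends wholly on assumed rates and one-for-one substitution.

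Only secondary and economic outcomes are affected. The primary outcome (CCQ recovery time), its sample size, and the counts of admissions, hospital days and emergency visits do not depend on nurse contacts. This is a cheap improvement, not a threat to the main conclusion.

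**What to change.** 1. Add scheduled and unscheduled visits and telephone calls to the respiratory or practice nurse to the utilisation list, in both arms.
2. Define the contact in the cost-effectiveness ratio so that it includes these, and include their cost under direct health care.
3. Collect them through the existing four-weekly calls and record review. Ask about nurse telephone calls explicitly in the four-weekly call, because records of visits may not show them.
4. Book the two reinforcement calls, made only in the intervention arm, under programme implementation, and keep them out of the contact count.

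The cost is one extra item in data collection that already takes place. The utilisation result may look less favourable to the Action Plan. Nothing changes for the primary outcome.
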